### Adverse events reporting

All adverse reactions and serious adverse events (SAEs) reported spontaneously by the subject or observed by the investigators or other staff members will be recorded by the research team. A SAE is an undesirable experience occurring to a subject during the study, whether or not considered related to the research procedure. Although it is unlikely that SAEs would occur given the nature of the intervention, all adverse events and SAEs will be reported to the local independent advisory board. This board will consist of the supervisor, the study coordinator and an independent medical professional from the local health facility. The chair or a nominated person from the advisory board will review SAEs within 48 h and the advisory board will review all AEs twice a month and where necessary to determine any appropriate action in respect of ongoing trial conduct. On the informed consent form, patient information is included to inform participants that the field coordinator, or another clinician other than their therapist are available to them if they are upset by this study.

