### The Problem Management Plus (PM+) program

The WHO PM+ program involves a set of a brief psychological strategies that seek to ameliorate symptoms of common mental health problems (e.g. depression, anxiety, stress). The intervention protocol was written for WHO by a consultant of the University of New South Wales, Australia [12, 16].

The PM+ intervention protocol has been translated into Kiswahili and adapted to the local sociocultural context of the lives of women in poor neighborhoods of Nairobi. The translation and adaptation have been reviewed in two workshops: one with experts on the intervention and the other with community representatives including local leaders, local health care provides, community health workers (CHWs) and Kenyan translators [17].

PM+ integrates problem-solving and behavioral treatment techniques that demonstrate amenability to low-intensity delivery and are evidence-based [18–21]. PM+ is delivered over 5 weekly sessions of 90 min duration. Clients are systematically taught four strategies: (1) stress management; (2) problem solving; (3) behavioral activation and (4) skills to strengthen social support. The PM+ program is being made available in different formats. In the current RCT, the PM+ individual version will be tested.

PM+ providers will be female CHWs, who will be selected based on individual interviews. PM+ providers will meet the following criteria: (1) High school diploma (form 4 level of education or above); (2) Reasonable proficiency in both Kiswahili and English language; (3) 1-year training post-secondary school as CHWs or health related career; (4) 2-years and above experience in community work; and (5) Already working as a CHW within a given geographical area. PM+ providers will receive a total of 2 weeks of training. In addition, one professional Kenyan supervisor will be employed for each of the three health facility areas.

Protocol adherence will be ensured by the supervisors and weekly group supervisions of the CHWs [22]. Supervisors will receive weekly supervision and on-the-job training in supervision skills by the project intervention consultant ([name]).

To evaluate treatment fidelity, 10 % of all PM+ sessions will be attended by the supervisor, using a checklist to ensure basic elements of the PM+ intervention have been followed as required.

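### The SAE definition has no seriousness criterion, so SAEs and AEs and their two review timelines cannot be told apart; passive event capture may also be uneven between arms

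*Protocol article*

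**What the plan says.** All the text on event definition, recording and review is in one section of the protocol article, Adverse events reporting.

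- **Definition.** "A SAE is an undesirable experience occurring to a subject during the study, whether or not considered related to the research procedure". No other definition of an SAE is given, and none of an AE.
- **Recording.** The events to be recorded are "All adverse reactions and serious adverse events (SAEs) reported spontaneously by the subject or observed by the investigators or other staff members". This gives two routes: the woman volunteers the event, or someone on the staff notices it.
- **Reporting.** The section adds that "all adverse events and SAEs will be reported to the local independent advisory board", and remarks that SAEs are not expected, given the kind of intervention.
- **Review.** Two timelines follow. For SAEs: "The chair or a nominated person from the advisory board will review SAEs within 48 h". For AEs: "the advisory board will review all AEs twice a month and where necessary".

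Staff contact is described elsewhere. Under The Problem Management Plus (PM+) program, "PM+ is delivered over 5 weekly sessions of 90 min duration". Under Enhanced treatment-as-usual (ETAU), control women are referred to primary care nurses who have had a three-day training, with no number of visits stated. Under Procedure, both arms are interviewed by blinded assessors 7 weeks and 20 weeks after inclusion. Table 1 lists no adverse-event questions at either interview. The Analysis section plans between-group models for GHQ, WHODAS and PSYCHLOPS and mentions no comparison of harms.

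**The concern.** An SAE definition has to say what makes an event serious. The sentence given covers occurrence and relatedness only, and so fits any adverse event. This is not a detail left to a fuller document: the article states a definition, and the definition is wrong for the term it defines. The two review timelines depend on it. Staff following the text have no rule for deciding which events need review within 48 hours and which can wait for the twice-monthly review.

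The second matter is smaller. When events enter the record only by being volunteered or noticed, the count depends partly on how often someone is there to hear or see them. One arm has five fixed sessions with a provider, and the other has an open number of nurse visits. If event counts were later set side by side by arm, part of any difference could reflect opportunity to record. In this population the events of interest, such as further violence or suicidal crisis, are ones a woman may not volunteer unprompted.

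**Working it through.** **Part A: the definition (no arithmetic applies).**

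1. The stated SAE class is every undesirable experience during the study, related or not.
2. An AE is not defined, but it cannot be wider than that class. Hence every AE satisfies the SAE definition.
3. SAEs go to 48-hour review and all AEs to twice-monthly review. By step 2 every event qualifies for both, so the text does not sort events.
4. The section calls SAEs unlikely. Under Participants, women enter with GHQ-12 above 2 and WHODAS above 16, and they are followed for 20 weeks. Undesirable experiences of some kind must be expected in such a sample. The remark makes sense only for a narrower class of event, which the section does not define.

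**Part B: how uneven recording could be (illustration only).** The documents give no event-recording figure to reproduce.

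Inputs from the article: 2 interviews after baseline in both arms (weeks 7 and 20) and 5 PM+ sessions. The fifth session falls one week before the week-7 interview and sessions are weekly, so they fall at weeks 2, 3, 4, 5 and 6.

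Assumed inputs: equal true event risk; a probability q that an event is recorded at any one later contact; and k nurse contacts in the control arm that feed the trial's event record.

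*Simplest case: every event precedes all contacts.* Recorded share = 1 − (1 − q)^m, with m = 7 in PM+ and m = 2 + k in control. For q = 0.10 and k = 0: 1 − 0.9^7 = 0.522 and 1 − 0.9^2 = 0.190, ratio 2.75.

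| q | PM+ share | Control k=0 (ratio) | k=1 (ratio) | k=2 (ratio) | k=5 (ratio) |
|---|---|---|---|---|---|
| 0.10 | 0.522 | 0.190 (2.75) | 0.271 (1.93) | 0.344 (1.52) | 0.522 (1.00) |
| 0.20 | 0.790 | 0.360 (2.20) | 0.488 (1.62) | 0.590 (1.34) | 0.790 (1.00) |
| 0.30 | 0.918 | 0.510 (1.80) | 0.657 (1.40) | 0.760 (1.21) | 0.918 (1.00) |

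*Allowing for timing.* An event can be recorded only at contacts after it. After week 7 both arms have one scheduled contact left, and that period is 13 of the 20 weeks. Take events uniform over 20 weeks, q = 0.10, k = 0:

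- PM+: weeks 0–2 have 7 contacts ahead (0.522). The five single weeks from 2 to 7 have 6, 5, 4, 3 and 2 ahead (0.469, 0.410, 0.344, 0.271, 0.190). Weeks 7–20 have 1 ahead (0.100). Share = (2×0.522 + 0.469 + 0.410 + 0.344 + 0.271 + 0.190 + 13×0.100)/20 = 4.03/20 = 0.201.
- Control: (7×0.190 + 13×0.100)/20 = 2.63/20 = 0.132 (0.1315 unrounded).
- Ratio = 0.201/0.1315 = 1.53.

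The same sums give 0.351 against 0.256 (ratio 1.37) for q = 0.20, and 0.469 against 0.374 (ratio 1.26) for q = 0.30. All of these still assume no nurse contacts.

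**The case against.** The best reply on the definition is that the literal reading errs on the safe side: if every event is an SAE, every event is reviewed within 48 hours, and all events reach the board anyway. That is fair. It rules out saying that the 48-hour review cannot be carried out; it could be, for everything. But then the twice-monthly tier has no events of its own and the remark that SAEs are unlikely has no meaning, so the wording still fails.

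On recording, several stronger readings are tempting and are not supported.

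- *Events are captured only if women volunteer them.* The section also records events that staff observe. The ETAU section expects severe problems to be noticed during control treatment or at study assessments.
- *The comparison of harms between arms is biased.* No such comparison is planned in the article. Uneven recording is a risk if harms are later reported by arm.
- *PM+ has seven contacts against two, hence 52% of events recorded against 19%.* This sets nurse follow-up at zero and places every event before the first session. Neither is stated, and timing alone brings the figures to about 20% against 13%. Even the direction is open: with more than five nurse contacts feeding the record, it would reverse in the simplest case.

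The article also provides some even-handed data. The Life Events Checklist, which covers events such as rape and serious injury, is repeated in both arms at follow-up, and Other measures says it will be reworded to cover the time since entry. Symptom scales and service-use items are likewise collected in both arms. This stands as mitigation. The checklist is not linked to event recording, however, and the violence instrument is given at baseline only.

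A reader might also question the board's independence, since "This board will consist of the supervisor, the study coordinator and an independent medical professional from the local health facility". The membership is openly stated and includes an independent clinician, and nothing shows who would chair it or do the 48-hour review. Changing the chair or the voting is a governance preference, not an error in the plan.

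**Conclusion.** The definition is wrong as written. It has no seriousness criterion, so it does not separate SAEs from AEs, the two review timelines cannot be told apart, and it conflicts with the section's own expectation that SAEs will be rare. This follows from the text alone and needs no assumption.

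The recording point holds in a limited form: ascertainment may be unequal if harms are reported by arm. Its size cannot be derived, because the number of control-arm nurse contacts, and whether those nurses report to the research team, are not stated. Under the assumptions shown, with q between 0.10 and 0.30 and events spread evenly over 20 weeks, the ratio of recorded events would be about 1.5 to 1.3 with no nurse contacts. It would be 1.00 if control women had five contacts on the same schedule that fed the record equally well.

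This is worth correcting because it concerns safety and is cheap. It changes no efficacy analysis, power statement or sample-size figure.

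**What to change.** 1. Use the present sentence as the definition of an AE. Define an SAE as an AE that meets standard seriousness criteria: death, threat to life, hospitalisation, lasting disability or another medically important event. The two existing review timelines then each have a clear set of events.
2. Use the same terms throughout the section. At present the recording sentence names adverse reactions and the reporting sentence names adverse events.
3. Add one short, identical adverse-event question set for both arms at the existing 7-week and 20-week blinded interviews. Base any by-arm reporting of harms on those answers. Keep volunteered and observed events for ongoing safety review.

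The cost is a wording change plus a few extra minutes in two interviews already planned, with no new visits or staff.

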### Enhanced treatment-as-usual (ETAU)

Treatment-as-usual in primary healthcare centers in Nairobi, Kenya to individuals with common mental disorders usually consists of no or placebo treatment. For this study, treatment as usual will be substantially enhanced. Participants in the ETAU group will be referred to their primary care clinicians (usually nurses) for follow-up. These primary care nurses will have received a 3-day training; 1 day on basic psychological first aid communication skills and building on this with training from the International Federation of Red Cross non-specific lay-counselling resource [23]. This resource focuses on ethical considerations for lay counsellors, structuring a helping conversation and referral for high care.

We will seek to keep track of the types and amount of support participants receive through the SRI. If, during this treatment or during the study’s assessments participants in ETAU arm show severe psychiatric disorders or problems (e.g., psychosis or suicidality) that require immediate specialist treatment and follow-up, they will be referred to the subcounty hospital, which has been contracted to provide gratis care to the participants referred for these problems.

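### The safety board is called independent, but two of its three members are study staff, and the 48 h SAE review need not involve the one independent member

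*Protocol article*

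**What the plan says.** All of the safety oversight described is in the protocol article, under Adverse events reporting. It states that "all adverse events and SAEs will be reported to the local independent advisory board". The next sentence gives the membership: "This board will consist of the supervisor, the study coordinator and an independent medical professional from the local health facility".

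Review then has two steps. For the first, "The chair or a nominated person from the advisory board will review SAEs within 48 h". For the second, the board as a whole goes through all adverse events twice a month and, where needed, settles what should follow for the conduct of the trial.

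The title of supervisor is explained only under The Problem Management Plus (PM+) program. There, "one professional Kenyan supervisor will be employed for each of the three health facility areas". On the role itself, the section says "Protocol adherence will be ensured by the supervisors and weekly group supervisions of the CHWs". For the fidelity check, 10% of "PM+ sessions will be attended by the supervisor, using a checklist".

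**The concern.** An independent safety board is meant to have serious events looked at by people with no responsibility for the intervention or for keeping the trial running. Here the label and the membership stand in consecutive sentences and do not agree.

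Two things are at stake. First, a woman in the PM+ arm may have a serious event, and the first person to review it may be someone responsible for how PM+ is delivered. Second, when the board considers whether the trial should change, most of those present are study staff. The article itself foresees psychosis or suicidality during the study (under Enhanced treatment-as-usual), so the arrangement may well be used. If PM+ is found effective, the plan is to roll it out, and its safety record will then be read as having been independently reviewed.

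**Working it through.** No formula applies. The check compares the board's membership with the roles described elsewhere in the article.

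1. **The supervisor.** Adverse events reporting says only *the supervisor*, so the identity has to be inferred. The PM+ program section is the one place that employs people under that title. It makes them answerable for PM+ adherence and has them attend sessions with a fidelity checklist. Assessors are overseen by someone with a different title, the trial manager (Procedure). The PM+ supervisor is therefore the natural reading. If another study supervisor were meant, that person would still be study staff.

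2. **The study coordinator.** The title places this person in the running of the trial. The article does not call the role independent.

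3. **The medical professional.** Described expressly as independent, and drawn from the local health facility. I take that description at face value.

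4. **Count.** Study staff: 1 (supervisor) + 1 (coordinator) = 2 of 3. Described as independent: 1 of 3. The article employs three supervisors, one per area, but lists one on the board. It does not say which one, or whether each area has its own board. The count is 2 of 3 for any board so composed.

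5. **The 48 h step.** The reviewer is the chair or a nominated person. The chair is not identified. Any of the three members could therefore be the reviewer, and two of those three choices involve no independent person at this step.

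6. **The twice-monthly step.** The whole board reviews all adverse events, and SAEs are among them. The independent member should therefore see each SAE, but possibly only at the next of these meetings. Action on trial conduct belongs most naturally to this step. No voting rule is given. If the three members have equal say, study staff can carry a decision 2 to 1.

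The independent member is thus present on the board, but the text guarantees that person neither the first look at an SAE nor a decisive voice afterwards.

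**The case against.** The strongest defence has four parts.

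- **The board as a whole does review events.** A reader might infer that a supervisor can decide alone what follows from a serious event. The text does not support that. The single reviewer has only the 48 h review, and action on the trial sits most naturally with the full board, which includes the independent member. This limits the concern to who looks first and who holds the majority.

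- **No causality judgement is described.** A reader might infer that harm from PM+ would be attributed too rarely and never corrected. The article gives the board no relatedness assessment, and it defines an SAE whether or not the event is thought related to the research. Nor does it show that any review was biased. That inference fails.

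- **The third member is called independent.** A reader might infer a stake in the comparator, because "Participants in the ETAU group will be referred to their primary care clinicians (usually nurses) for follow-up" and the medical professional comes from a health facility. Nothing says that this person delivers the comparator. Such a stake would in any case push towards blaming PM+, not towards excusing it.

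- **This is a condensed article.** Who chairs, rules on recusal and onward reporting to the ethics committees may stand in a full protocol that is not shown, so their absence is no fault by itself. It is also unstated that the board's supervisor oversees the community health worker concerned, or that every member knows the arm.

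These points narrow the concern but do not remove it. The label and the membership are both stated in this article, and one independent member out of three does not make the board independent.

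**Conclusion.** The point holds as a mismatch between a stated property and a stated composition. Two of three members are study staff, the 48 h SAE review can be done without the independent member, and study staff form the majority when trial conduct is considered.

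It rests on two assumptions. The first is that *the supervisor* is the PM+ supervisor. This is well supported but inferred, and without it the member is still study staff. The second is that members have equal say, since no voting rule is given.

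The point touches no outcome, sample size or analysis, and no SAE rate is given from which to put a number on the consequence. It deserves correction because it concerns safety oversight and costs little.

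**What to change.** Keep the board and its three members, and add two sentences to Adverse events reporting and to the board's terms of reference:

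- The independent medical professional chairs the board and carries out, or must countersign, the 48 h review of every SAE.
- The supervisor and the study coordinator supply information, but neither may be the nominated reviewer, and together they may not outvote the independent member on action affecting the trial.

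If this is not adopted, stop describing the board as independent.

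The cost is small: the independent member must be reachable within 48 h. The change adds no visits or data. Recruiting another clinician from outside the three facilities is not needed to cure the mismatch, because the existing member is already described as independent.

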### Ethics

The project has been approved locally by the Research Ethics Committee of the Great Lakes University of Kisumu, Kenya and by the WHO Ethical Review Committee (Protocol ID: RPC656, April 25, 2014, Amendment February 16, 2015).

## Discussion

By evaluating the effectiveness of PM+ in women affected by gender-based violence in Nairobi, Kenya, we seek to address the need for access to brief, effective psychological interventions that can be administered by non-professional health workers in LMICs. A second RCT on the effectiveness of individually delivered PM+ in males and females in an humanitarian setting in Peshawar, Pakistan is underway [33]. If proven effective, PM+ may not only be used in similar areas in Kenya and Pakistan, but rolled out to other affected areas in both LMIC settings and high-resource countries for further adaptation. It may be a useful intervention for humanitarian settings (e.g., conflict settings) where mental health care for GBV-survivors is often lacking. PM+ may be tested in different formats (e.g., internet-delivered, group or young adolescent version) across a variety of populations suffering from psychological distress. The PM+ manual and accompanying training materials, if proven effective, will be published by WHO and will be made available on WHO’s website, in order to enable future scaling-up.

## Abbreviations

WHO: World Health Organization
PM+: Problem Management Plus
RCT: randomized controlled trial
GBV: gender based violence
WHODAS: WHO Disability Assessment Schedule 2.0
GHQ-12: General Health Questionnaire-12
SRI: Service Receipt Inventory
ETAU: enhanced treatment as usual
PTSD: posttraumatic stress disorder
LMIC: low and middle income country
CBT: cognitive behavioural therapy
PCL-5: PTSD checklist for DSM-5
WHO-VAW: WHO violence against women instrument
LEC: life events checklist
PSYCHLOPS: psychological outcome profiles instrument
CHW: community health worker
HLM: hierarchical linear modeling
SPSS: statistical package for the social sciences
SAE: serious adverse event
